### Recruitment

An initial telephone interview screens out those people whose participation in the study is motivated by problems other than their mood. The potential subjects then undergo a clinical evaluation, performed by doctoral-level clinical psychologists certified by the Romanian Board of Psychologists, and currently supervised in their activity by senior psychologists. They have been trained in using the SCID [37] as part of their clinical program, at Babes-Bolyai University. Additionally, for the purposes of this study, all of them received specific practical training in administering the SCID modules used in the current protocol. To ensure the adequacy of the assessment procedure, all the initial clinical evaluations are audio recorded and randomly verified by a senior clinical psychologist. Moreover, all the potential eligible cases are discussed with the same senior clinical psychologist before enrolment. Every evaluation is audio recorded, to allow for reliability checks for depression diagnoses, performed by an independent evaluator, on 25% of randomly selected interviews. SCID [37] and BDI-II [24,29] (see above) are used for purposes of evaluating eligibility.

Prospective participants are recruited into the treatment study by clinical psychologists at the Babes-Bolyai University Psychological Clinic. Potential participants are also referred by psychiatric clinics that collaborate with Babes-Bolyai University as well as by private practices. Additionally, media avenues (for example, local newspapers, radio, social networks) as well as posters and fliers are used for recruitment purposes.

#### Assignment to interventions

The participants are randomly assigned to one of the two conditions using a sequence generated by the software Randomizer.org. Randomization is performed by a research assistant using a simple (unrestricted) randomization sequence that assigns two unique numbers per participant; the number assigned is either 1 or 2, according to the number of experimental conditions. To conceal the allocation mechanism, the same research assistant puts the patient in touch with their therapist without revealing anything about the intervention protocol to be implemented by that therapist.

The CT and ED-CT therapy protocols are each delivered by two different psychotherapists. All four psychotherapists are certified by the Romanian Board of Psychologists, and have extensive training in CT, completed through the Romanian Association of Cognitive and Behavioral Psychotherapies. The two psychotherapists delivering the ED-CT protocol have received additional training in the evolutionary components of the ED-CT protocol. Under the direct supervision of the principal investigator, the therapists have undergone 6 weeks of training, following the protocol manual for the ED-CT group.

The principal investigator and the statisticians running the data analysis will remain blinded to the experimental condition until the completion of the study.

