#### Participant timeline

For the study, potential participants are provided with verbal and written information during the first appointment with a clinical psychologist. Written consent for the participation in the clinical evaluation part of the study is sought at this time. A second appointment is scheduled, in which the respondents are evaluated clinically. If the inclusion criteria are met, written consent for participation in the treatment part of the study is obtained, within a 2-week interval.

The participants are then randomized by a research assistant to receive either: 1) ED-CT or 2) CT, without being informed about their group allocation (see flowchart in Figure 1). Randomization is performed *a priori* using a computer software package (http://www.randomizer.org). In addition, the clinical psychologists who perform the clinical assessment are blinded to the experimental condition through the entire duration of the study. Participants who do not meet the criteria for the study are referred to the Babes-Bolyai Psychological Clinic or to a psychiatric clinic in Cluj-Napoca.

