### Trial status

Participant recruitment began on September 1, 2012. Randomization of the participants was performed on September 27, 2012. The first participant was enrolled on October 3, 2012.

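### The step described as allocation concealment is participant masking; no described step keeps the next assignment from the assistant who both randomises and assigns

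*Protocol article*

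**What the plan says.** Four sections of the protocol article bear on this.

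- **Assignment to interventions.** On who randomises and how: "Randomization is performed by a research assistant using a simple (unrestricted) randomization sequence". On concealment: "To conceal the allocation mechanism, the same research assistant puts the patient in touch with their therapist", and this is done "without revealing anything about the intervention protocol to be implemented by that therapist". Each protocol has its own two therapists, four in all, and only the ED-CT pair had the extra evolutionary training. The principal investigator and the statisticians are to stay blinded until the study is complete.
- **Participant timeline.** After eligibility and treatment consent, "The participants are then randomized by a research assistant to receive either" ED-CT or CT, "without being informed about their group allocation". The next sentence says that randomisation is done a priori, "using a computer software package". The psychologists who carry out the clinical assessment are blinded to condition throughout.
- **Sample size.** One hundred participants were randomised. After the random numbers had been generated, the team chose to use the first sequence, which gave 43 CT and 57 ED-CT.
- **Trial status.** Recruitment opened on 1 September 2012. "Randomization of the participants was performed on September 27, 2012". "The first participant was enrolled on October 3, 2012".

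**The concern.** Allocation concealment means that whoever enters or assigns a patient cannot know the next arm until that patient is irrevocably in the trial. Masking is a different safeguard: it keeps the arm from the patient or the assessor once it has been decided. The article names one step as concealment, and that step is of the second kind.

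The distinction matters because simple randomisation from a list made in advance is unpredictable only while the list stays hidden. If the person who links patients to therapists can see it, the order or choice of linkage can be influenced by a patient's apparent prognosis. The resulting difference between arms exists at baseline. Masking the outcome assessors does not remove it, and a larger sample does not dilute it if the same fraction of patients is steered.

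**Working it through.** **1. What the named step does.** It withholds the treatment protocol from the patient, at the point of contact with the therapist, when the arm is already settled. This repeats the participant masking already given under Participant timeline. It leaves untouched the information available to the assistant before assignment.

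**2. Who does what, as stated.**

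| Step | By whom | Safeguard stated |
|---|---|---|
| Recruitment and eligibility evaluation | Clinical psychologists; eligible cases discussed with a senior psychologist | Assessing psychologists blinded to condition |
| Generation and choice of the sequence | Software; first sequence chosen by the team | None described |
| Randomisation | Research assistant | None described |
| Link to a therapist | The same research assistant | Patient not told the treatment protocol |

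Each therapist delivers one arm, so the link to a therapist is the assignment. The second and third rows are where concealment would have to act.

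**3. Timing.** The randomisation date (27 September 2012) is 6 days before the first enrolment (3 October 2012). Participant timeline places randomisation after eligibility and consent, but also says it is done a priori. The sections agree if 27 September is the day the list was generated and each patient was matched to it later. Sample size and Trial status instead speak of the participants themselves as having been randomised.

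**4. The plan's own effect size, used as the yardstick.** Inputs from Sample size: f = 0.247, two measurements (m = 2), correlation ρ = 0.50, α = 0.05, N = 100. For the between-groups test in repeated-measures ANOVA,

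λ = f²·N·m / (1 + (m − 1)ρ) = 0.061009 × 100 × 2 / 1.5 = 8.13,

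with 1 and 98 degrees of freedom, which gives power 0.806. An N of 98 gives 0.798, so 100 is the smallest even total that reaches 0.80 and the stated figure reproduces. The matching standardised difference is d = 2f = 0.494.

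**5. Illustrative size of a bias.** The inputs here are assumptions, since the documents give none. Suppose k patients with better prognosis go to one arm and k with worse prognosis to the other, each 0.5 SD from average and each in place of an average patient. Then

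shift = 0.5k/57 + 0.5k/43.

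| Patients steered (2k) | Shift (SD) | Share of d = 0.494 |
|---|---|---|
| 4 | 1/57 + 1/43 = 0.018 + 0.023 = 0.041 | 8% |
| 10 | 2.5/57 + 2.5/43 = 0.044 + 0.058 = 0.102 | 21% |

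The shift is proportional to both the number steered and the assumed prognostic distance.

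**6. The 43/57 split.** Under simple 1:1 randomisation of 100, a split at least this uneven has two-sided probability 2·P(X ≥ 57) = 0.193.

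**The case against.** The strongest reply is that this is a condensed article. Custody of the list, envelopes and release rules commonly sit in a full protocol, and their absence here proves nothing. That is right as far as it goes, and no weight is placed on the absence alone. But the article does name a concealment step, and the step named does not conceal. That is a matter of what is stated.

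Three further objections stand and limit the point.

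- A reader might infer that the assistant holds an open list, knows every upcoming assignment and controls the order of entry. No section says so. Psychologists recruit and evaluate, cases are discussed with a senior psychologist before enrolment, and the assistant appears only after consent. The assessing psychologists and the principal investigator are stated to be blinded, which partly protects the eligibility decision. It does not reach the assistant's own step.
- A reader might infer from the dates that patients were allocated before they entered. The a priori sentence in Participant timeline largely resolves this, and generating a list before enrolment is ordinary practice. What remains is loose wording.
- A reader might take 43/57 as a sign of interference. A probability of 0.193 gives no support for that.

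The bias figures can fairly be called arbitrary: both the number steered and the 0.5 SD are chosen, so they are shown only as a range.

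**Conclusion.** The point holds in a limited form. The article labels participant masking as allocation concealment. One research assistant performs the randomisation from a sequence generated in advance and also makes the link that determines the arm, and no described step hides the next assignment from that person. This is a stated procedure that does not conceal; it is not evidence of subversion. Foreknowledge by the assistant remains an inference from the combined role.

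The size of any bias cannot be determined from the document. Under the assumptions shown, it would be about 0.04 to 0.10 SD, and it would be zero if nobody was steered. The wording on dates should be tidied so that a reader can verify that each patient's entry preceded allocation.

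**What to change.** **For patients still to be entered.** Have the sequence held by existing staff who have no contact with patients or therapists, or place it in the existing electronic data system with access closed to the assistant and the therapists. The access restriction is needed because Data collection, management, and analysis has therapists helping patients to use that system. Release each allocation only once eligibility, treatment consent and baseline BDI-II are time-stamped.

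**In the text.** Under Assignment to interventions, describe the present step as participant masking. Under Sample size and Trial status, separate list generation from patient allocation, so that 27 September 2012 is given as the date of the list.

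**In reporting.** Give each patient's own allocation date, including for those already entered. This and the rewording remain useful if enrolment is already complete.

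**Cost.** A small change in who holds the list, plus a time stamp in a system already built. The article does not describe staffing in enough detail to show who could take custody, so the team should confirm that someone suitable is available.

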### Data collection, management, and analysis

Each eligible patient is assigned a unique identification number and asked to complete the evaluation package, including the primary, secondary, and other outcomes, as well as demographic information (initial assessment). The same set of measures is administered after the final session (post-intervention assessment) and at 3 months after the final session (follow-up assessment). After sessions 4 and 8, patients also complete several measures of primary outcomes (that is, BDI-II), and other outcomes (ATQ, DAS, ABS II, PANAS, B-COPE, treatment outcome expectancies,WAI, CSQ-8, and Intent-to-Attend Scale). In addition, the participants complete the BDI-II, CSQ-8, and Intent-to-Attend Scale after each session.

To ensure high accuracy of data collection, all the measures are completed electronically, via a special system designed to reliably capture and organize the data points while minimizing the risk of missing responses. The system has been especially developed for the purposes of this study, and is secured on a server. Each participant uses their unique identification number to log on to the system. The therapists are responsible for assisting the patients in this process, and providing clarifications when needed.

To promote participant retention and follow-up completion, several strategies are being used. First, the participants receive a clear and complete description about the project, including, but not limited to, information regarding the type of psychotherapy offered, that is, CT, which is the standard of care in the psychological treatment for depression, having remission rates comparable with medication, and being more efficient than medication alone in the long term. The participants are also informed that the treatment is being provided free by therapists trained in the top-ranked Department of Clinical Psychology and Psychotherapy in the country [96], recently added, through its academic spin-off, the International Institute for the Advanced Studies of Psychotherapy and Applied Mental Health, to the Mapping of the European Research Infrastructure Landscape (MERIL) network [97]. Because in Romania psychotherapy sessions are not reimbursed by health insurance companies, we expect that this financial factor will also act as a motivator for the patient to stay in treatment. Furthermore, the therapy sessions are scheduled in a flexible manner, according to the patient’s preferences. Additionally, the therapist will call the participant the day before the planned session for a brief check, and to ensure continuation in therapy. Most importantly, to ensure retention, at the end of each session the participants complete the ‘Intend-to-Attend’ one-item scale, which is meant to promote commitment to the therapeutic process as well as to detect any issues that might require the therapist’s special attention. Lastly, the therapists carefully prepare the end session of the therapy and explain to the participants that they will keep in touch. The therapists also remind the patients at this time that the free treatment was possible because of a research grant, which makes the collection of follow-up measurements essential.

The severity of, and improvement in the BDI-II scores within and between the groups will be examined using mixed-effects linear regression analysis with a random intercept and slope over time (four assessments: baseline, after sessions 4 and 8, post-treatment) and fixed effects for treatment assignment.) The 3-month follow-up data will be analyzed in a separate mixed-effects model. The main analysis will compare groups in terms of depression level (that is, diagnostic status and symptom intensity). Results on the other measures will be investigated in an exploratory manner. When analysis of secondary/other outcomes are performed, the error probability will be adjusted according to the number of group comparisons performed [98].

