**CONSORT flow diagram**[94]**showing subject allocation to the therapy conditions.**

### Sample size

An *a priori* power analysis based on a medium effect size estimation indicated that a total of 100 participants are needed (planned main statistical test is ANOVA (repeated measures, between factors); *f* effect size: 0.247; statistical power: 0.80; α error probability: 0.05; two groups, two main measurements (pre-intervention and post-intervention); correlation between repeated measures: .50). Power analysis was computed using the G*Power 3.1.6 program [95]. Consequently, we randomized a total of 100 participants. Following generation of the random numbers, we decided to use the first sequence of numbers for the participants’ allocation to the groups. This resulted in 43 participants randomized to the CT group, and 57 participants randomized to the ED-CT group.

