### Ethics and dissemination

The study has been approved by the ethics commission at Babes-Bolyai University. As with any study on depression, there are ethical concerns that need to be addressed. First, the exclusionary criteria exclude people who pose an imminent danger to themselves or others. These people will be immediately referred to the appropriate services dealing with such cases. Second, if a patient’s condition worsens during the therapy, the supervising clinical psychologist can opt to terminate the treatment ahead of schedule and make an appropriate referral. Third, people with mental conditions other than depression are also excluded, and will be referred to the services best suited to dealing with their problems.

One arm of this clinical trial involves interventions that stem from an evolutionary understanding of human behavior. The role of the SCSRFQ scale, administered at intake, is to assess the strength of religious beliefs before the first session, when the ED-CT conceptualization takes place. Special care will be taken with the patients whose religious beliefs might make them less receptive to the theoretical framework of such interventions. In such cases, the therapist will be mindful of the patient’s beliefs, and explain the basic tenets of ED-CT in a very sensitive manner.

Finally, confidentiality and privacy are of paramount importance. The completed forms of the clinical instruments are kept in locked cabinets and the access to the electronic data is password-protected. The passwords are changed regularly, and the clinical assessment reports contain no identifying information.

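### Post-treatment and follow-up assessments are triggered by the final session, so a patient who stops early has no fixed outcome date; the stated 0.80 power also assumes no loss

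*Protocol article*

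**What the plan says.** **Timing of outcomes.** The section on data collection, management and analysis states: "The same set of measures is administered after the final session (post-intervention assessment) and at 3 months after the final session (follow-up assessment". It repeats the BDI-II, but not the SCID, after sessions 4 and 8, and also collects the BDI-II after every session. No post-baseline assessment is given a time from enrolment, baseline or the first session.

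**Treatment course.** Under Interventions, both arms have 12 weekly sessions. The data collection section adds that "the therapy sessions are scheduled in a flexible manner".

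**Early stopping.** Under Ethics and dissemination, if a patient worsens, "the supervising clinical psychologist can opt to terminate the treatment ahead of schedule and make an appropriate referral". Monitoring study implementation gives the supervisor the same power and defines harm as a clinically significant rise in the BDI-II.

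**Outcomes and analysis.** The primary outcomes are depressive symptoms and a categorical diagnosis after treatment, measured by BDI-II and SCID. BDI-II goes into a mixed model over four assessments (baseline, sessions 4 and 8, post-treatment). The 3-month data have a separate model. Diagnostic status is part of the main analysis.

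**Sample size.** The sizing test is given as "planned main statistical test is ANOVA (repeated measures, between factors", with "effect size: 0.247; statistical power: 0.80; α error probability: 0.05", "two groups, two main measurements (pre-intervention and post-intervention" and "correlation between repeated measures: .50". The calculation asked for 100, and the text continues: "Consequently, we randomized a total of 100 participants". The split was 43 CT and 57 ED-CT. The article states no allowance for loss.

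**The concern.** An outcome visit defined by attendance is well defined only for patients who attend to the end. Here the protocol itself provides for patients who will not, and one route out depends on the outcome, since a rise in BDI-II can lead to termination. The patients whose post-treatment status is least certain to be recorded thus include those doing badly.

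At stake is whether every allocated patient has a comparable post-treatment diagnosis and 3-month follow-up. If not, the SCID comparison and the follow-up model rest on those who reached the trigger, or mix scores taken at different points in the course. Separately, the number randomised equals the number calculated, so any loss of outcomes comes straight off the power of the sizing test.

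**Working it through.** **1. Two readings of *final session*, applied to a patient who stops after session 5.** Assume one session a week, as planned, and take 3 months as about 13 weeks.

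- *Planned session 12.* The session never takes place, so nothing triggers the post-treatment BDI-II, the SCID or the follow-up.
- *Last session attended.* Post-treatment falls at about week 5 instead of week 12. Follow-up falls at about week 5 + 13 = 18 instead of 12 + 13 = 25. Both are 7 weeks early relative to a completer.

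Neither reading gives early stoppers and completers the same outcome time.

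**2. What is left for each outcome if the post-treatment visit is missed.**

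| Outcome | Patient leaves after session 3 | Patient leaves after session 6 |
|---|---|---|
| BDI-II mixed model | baseline only | baseline and session 4 |
| BDI-II per session (collected, not among the model's four assessments) | sessions 1–3 | sessions 1–6 |
| SCID diagnosis | baseline only | baseline only |
| 3-month follow-up | none | none |

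BDI-II is partly protected. SCID and follow-up are not.

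**3. How far the SCID comparison could move.** With a fraction *m* missing in each arm, the difference in remission rates is (1 − *m*) × observed difference + *m* × difference among the missing. The last difference lies between −1 and +1. The result can therefore move by ±*m* around the value obtained when missing patients are treated alike in both arms: ±5, ±10 and ±20 percentage points for assumed *m* of 5%, 10% and 20%. This is the general worst case for any trial, not an estimate for this one.

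**4. Reproducing the stated power.** Inputs from the Sample size section: f = 0.247, α = 0.05, m = 2 measurements, ρ = 0.50, N = 100. For the between-factors test, λ = f² × N × m / (1 + (m − 1)ρ), with 1 and N − 2 degrees of freedom.

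- 50/50: λ = 0.247² × 100 × 2 / 1.5 = 8.13, power **0.806**. N = 98 gives 0.798, so 100 is the smallest even total that reaches 0.80. The stated figure reproduces.
- 43/57: λ = (2f)² × (n₁n₂/N) × m / (1 + (m − 1)ρ) = 0.494² × (43 × 57/100) × 2 / 1.5 = 7.98, power **0.799**.

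**5. The same test at 43/57 with dropouts deleted.** Equal proportional loss *a* multiplies λ by (1 − *a*). The article gives no loss rate, so *a* is assumed.

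| Assumed loss | λ | Power |
|---|---|---|
| 0% | 7.98 | 0.799 |
| 5% | 7.58 | 0.778 |
| 10% | 7.18 | 0.755 |
| 20% | 6.38 | 0.704 |

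These values belong to the ANOVA used for sizing, which compares the average of pre and post between groups. They are not the power of the planned mixed model or of the SCID comparison.

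**The case against.** **The article may simply be condensed.** Weekly sessions for 12 weeks give the final session a nominal date. The text never says that non-attenders go unassessed, and visit windows may be in the full protocol. That stands as a reason not to claim that such windows do not exist. It does not remove the point, because the article does state a trigger, and on either reading that trigger gives early stoppers no comparable outcome date.

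**Flexible scheduling may mean only the day and hour within each week.** That is possible. The variation in completers' dates is therefore a lesser part of the point, which rests mainly on early stopping.

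**A reader might infer that the trial becomes a comparison of completers.** For BDI-II the documents do not support this. The mixed model can use the baseline, session 4 and session 8 scores of patients who later stop, and per-session scores are collected as well. The exposure is in the SCID and the follow-up.

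**A reader might infer that 100 patients cannot deliver the stated power, or that the protocol forecasts attrition.** Neither is supported. The calculation reproduces with complete data, and the article describes retention measures without forecasting a loss rate. The lower figures above rest wholly on assumed losses and on deleting dropouts.

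**Conclusion.** The point holds as a defect in the stated assessment rule. Tying the post-treatment and follow-up visits to the final session, while allowing early termination for worsening, leaves early stoppers with no outcome visit or one at an arbitrary time. It bears hardest on the co-primary SCID diagnosis and the follow-up model, and less on the BDI-II. Its size cannot be fixed from the article because no rate of early stopping is given.

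The sample size point is secondary. The power of 0.80 is correct for complete data and has no margin for loss: at 43/57, an assumed 5% loss costs about 2 percentage points in the sizing test and 20% costs about 10. The article should say that its figure assumes no loss. It does not follow that the trial is underpowered for its planned analyses.

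**What to change.** 1. Schedule the post-treatment BDI-II and SCID at a fixed time from the baseline assessment or the first scheduled session, corresponding to the nominal end of the 12-week course. Schedule the follow-up 3 months after that date. Apply both to every allocated patient, whatever their attendance. Time from randomisation is a poor anchor here, because Trial status dates randomisation to September 27, 2012, before the first enrolment on October 3, 2012.
2. Use the per-session BDI-II already collected as auxiliary data for patients whose outcomes are still missing.
3. State that the 0.80 power assumes no loss. If figures under loss are added, label the loss as assumed and name the test they belong to.

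**Cost.** An amendment to the wording, reminders, and some extra effort to reach non-attenders and complete their SCIDs with the existing blinded assessors. No new instrument is needed, and the rules for ending treatment are not touched.
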